### Interventions

Special trained physiotherapists will take care of the patients. All the involved physiotherapists in this study are used to treat older adults at their own home.

### Experimental intervention

The experimental intervention consists of a home-based exercise programme Test-and-Exercise (T&E) delivered by specially trained physiotherapists. The development of this programme was carried out in several successive phases. We first established a list of 48 physical exercises that train balance control, mobility and strength of the body as well as functional exercises. We then asked 63 older adults to perform these exercises and to evaluate the perceived difficulty of each exercise using items with five response options: (0 = “no difficulty”; 1 = “some difficulty”; 2 = “difficult”; 3 = “very difficult”; 4 = “too difficult, I don’t do it”) [54]. At the same time, observer physiotherapists evaluated the quality of the task (0 = “perfectly performed”; 1 = “good performed with light deviation”; 2 = “performed with moderate deviation”; 3 = “badly performed”; 4 = “not performed”). This reliability study showed sufficient reliability of both items to be used in older persons to monitor exercise difficulty regarding the concepts of *self-efficacy*, *self-confidence* and *empowerment* to increase the motivation and the self-confidence [55].

We then developed a first Android application containing videos of the physical exercises of the T&E programme in addition to the T&E exercise booklet. We integrated the self-perceived difficulty items so that the participants have to rate the difficulty of the task before they include them in their own home-based exercise programme.

After this, we conducted a feasibility-study in 2014–2015 [56] where 19 participants were randomized in two groups: Intervention group T&E and Control group Otago. The results of this feasibility-study allowed us to prepare this randomized controlled study.

The T&E programme is delivered in a booklet with pictures and task descriptions, and on a digital tablet. The current programme contains 50 physical tasks grouped under fourteen topics related to home objects or activities. Each topic contains three or four tasks, ranged according to increasing difficulty. Unlike usual home-based exercise programmes, the physiotherapists do not prescribe exercises: they help and coach the participants to build their own exercise programme while ensuring safety and security (see Table 2). The patient chooses the tasks he/she wants to do, does it once as “test” and evaluates the perceived difficulty. The rating of the perceived difficulty classifies the task in two groups of exercises: those that can be included in their programme and those that should not be included. The Fig. 1 shows how to use the perceived difficulty to build the exercise-programme.

**Table 2 Tab2:** The innovative elements of the T&E programme

The innovative elements of the T&E programme	
1. Empowerment/Self-efficacy	Patient express his needs and fixes his goals for his/her own exercise programme
2. Learning autonomy step-by-step	Physiotherapists coach patients to learn how to manage his/her exercise programme
3. Test before Exercise	The evaluation of the perceived difficult allows the construction of the exercises programme in security to be sufficiently challenging without being dangerous
4. No prescription of exercises	Based on the perceived difficulty of the exercises, the patients decide which exercises they include in their own programme
5. Retest regularly the tasks	The re-evaluation of the perceived difficulty allows to see the progression of the capabilities
6. Use of an Android application on digital tablet	The digital tablet permit the visualization of the tasks at any moment, as Test and as Exercise
7. Fifty physical tasks	llows choices and adaptation in long-term

**Fig. 1 Fig1:**
[figure not shown]
Recommendations for create your home-based exercise-programme

Physiotherapy treatment is focused on increasing motivation and exercise adherence, working on the self-efficacy, the self-confidence and the autonomy of the patients. The implementation of the T&E programme is planned with eight physiotherapy sessions and four phone calls in six months. At each session the physiotherapists revise the exercises execution, verify that the diaries are correctly completed and repeat the recommendations for the training. At each phone call, the physiotherapists ask about the exercises, if the patient encounter difficulties and encourage them to train themselves.

The physiotherapists for the implementation of the T&E programme are trained in a basic training of half a day. The training focuses on i) Encouragement of the autonomy of the participant, ii) The significance of the evaluation of the perceived difficulty, iii) The work as coach for the participant, iv) Stimulation for exercises adherence: not too much at the same time, but regularly, v) Safety of the environment where the patient will train, vi). All physiotherapists will participate in a yearly refresher course and experience sharing session.

### Control interventions

To evaluate the T&E programme, we will compare it with two established interventions.

The first intervention consists of the implementation of the Otago exercise programme (OEP) [57]. This programme was developed in New-Zeeland in the 2000’s to prevent falls in older adults. It contains 22 exercises: five for warming-up, five for muscle strengthening of the lower limbs and twelve for balance training. In addition, it recommends walking sessions between the training days. OEP shows significant results in reducing the risk of death and falling in older community-dwelling adults but moderate exercise adherence [34].

The physiotherapists that implement the Otago programme are trained in a half-day basic training. The training consists of information about the Otago programme and how to deliver it to the patients with the original recommendations of [name] and Robertson [57]. In this training emphasis is put on prescription and control of the exercises. The physiotherapists will adapt the programme at every home session. The implementation of the Otago programme is similarly planned as the T&E program: eight home session and four phone calls in six months. At each session the physiotherapists revise the exercises execution, verify that the diaries are correctly completed and repeat the recommendations for the training. At each phone call, the physiotherapists ask about the exercises, if the patient encounter difficulties and encourage them to train themselves.

The second intervention (“Helsana”) is considered as usual care. It consists of a booklet with safety advice and twelve exercise-cards for “Going safely”, as constructed by the Swiss health care insurance Helsana. Helsana agreed to the use of their programme in this study (no financial support was provided). It contains five exercises in sitting position; six exercises in standing position and one stand up exercise. This programme is self-directed. It has never been evaluated in a trial. Physiotherapists will demonstrate the programme during one home session while they explain the recommendations and they will do all the exercises with the patient to ensure the security. They will then call the patients four times in a six-week interval, to ask if they encounter problems with the exercises.

In cases where the practice of home-based exercises could potentially harm the patients, the local coordinator could exclude the patients of the trial.

The innovative elements of the T&E programme are set out in Table 2 and these are the main distinguishing factors between the experimental intervention and both control interventions.

Even though participation of the patient in his/her treatment is considered as important to improve self-efficacy and exercise adherence, the physiotherapists often tend to apply a paternalistic approach rather than involving the patient [58]. The T&E programme offers the opportunity to the physiotherapists to experiment with a new way to work with patients.

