### Recruitment, randomization, blinding and treatment allocation

Caregivers (medical doctors, nurses, physiotherapists) in partner hospitals, health-care centres and medical offices will recruit the participants. To achieve adequate enrolment to reach target sample size, we projected to enrol a quarter of the sample size in each region (101/region) for three years (from August 2016 to September 2019). In addition, the local coordinators will meet the recruitment partners twice a year. They will give a feed-back about the progress state on the trial and motivate them to continue the recruitment.

The local coordinators will verify the eligibility criteria (Table 1) at the home of the participants.

The final decision on inclusion or exclusion and randomization takes place after the baseline assessment. A researcher who is not involved in the study creates an allocation list with a computer generated random sequence using the command “ralloc” within Stata (StataCorp, college Station, Texas, USA), version 14.2. A block-randomization is executed stratified in groups of age (65–79; > 80 years old) and in risk of fall categories [51] (low-moderate; high). If a couple living in the same house will participate, both persons will be randomized in the same intervention group [52].

The randomization was integrated in the software for Research Electronic Data Capture (REDCap [53]) and is concealed to all members of the research team. The project assistant manually triggers the randomization after the baseline assessment. The local coordinators will take note of the allocation group in REDCap.

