### Outcomes

The primary outcome “falls incidence” and exercise frequency will be assessed prospectively and for twelve months with self-recorded monthly diaries. If a patient decides to stop his participation (completing monthly diaries and exercise training), the physiotherapist will ask him to participate at the intermediary or/and finale assessment. Physiotherapist-assessors who are unaware of group allocation (“blinded assessors”) will assess the secondary outcomes at baseline, at the six-month intermediary assessment, and at the twelve-month final assessment. All assessors are independent physiotherapists and specially trained to perform the assessments.

To ensure that the assessors remain unaware of the group allocation, patients are told not to talk about their treatment with the assessor.

The main outcome is the incidence of falls for twelve months. For this study we define a fall as “*an unexpected event in which the participant comes to rest on the ground, floor, or lower level, with or without injury*” as recommended in the systematic review of Hauer et al. [59]. The history of falls (number, circumstance (Where? *Inside OR outside;* When? *Day OR night;* How? *Describe shortly the event*) and severity) in the previous twelve months will be assessed at baseline. During the study, falls will be prospectively self-reported (number, date, circumstance and severity) in monthly diaries [60]. To ensure that the patients complete the diaries, the physiotherapists will check them at each visit and ask about the diaries during each phone call [59]. In addition, falls events (number, circumstance and severity) will be asked during the intermediary assessment and at the final assessment. The diaries will be sent to the coordinators. The coordinators will send them in PDF version to the project-assistant. She will enter the data in REDCap software once a month.

Secondary outcomes include severity of falls, fear of falling, gait, strength and balance and quality of life. They will be assessed at baseline, at the intermediary assessment and at the final assessment. They also include exercise-adherence. This outcome will be assessed at twelve months.

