### Statistical analysis

Descriptive statistics will be used to present group characteristics on age, sex, body mass index, base of support width (BSW) [86, 87], and history of falls, activity of daily live, physical activity habits, and risk factors for falls.

According to statistical criteria of termination of the trial, we have no predefined stopping rules because we are not expecting risks that are different in the groups (i.e. no adverse event stopping criteria).

We will use an intention-to-treat analysis based on all randomized patients, with missing values and dropouts replaced by multiple imputation methods, as recommended by current guidelines on randomized controlled trials [88].

The primary analysis will be done to test for the incidence of falls. We follow the proposition of Röhmel and Pigeot [89], who showed that superiority of the experimental group (“T&E” in our case) over the reference treatment (“Otago” in our case) can be tested after successfully demonstrating non-inferiority (if stated a-priori in the protocol). To simultaneously demonstrate superiority of E (T&E) to R (Otago) and R (Otago) to P(Helsana) as well as the non-inferiority of E (T&E) to R (Otago), we will use negative binomial regression [90, 91] and follow an approach proposed by Mütze et al. [84]. A sensitivity analysis without multiple imputations of missing values will be performed.

For the primary analyses, we will adjust for the participants’ length of observation, center, age and risk for falls category [92]. We will perform a per protocol sensitivity analysis including time varying co-variables to reduce confounding and selection bias, e.g. due to differential censoring.

Further analyses will be performed to test the secondary endpoints quality of life (Overall score of OPQOL-35), severity of falls (Schwenk Scale), fear of falling (FES-I), functional capacities (TUG, FSBT, FTSTS, FR and SMWT), as well as adherence to the exercise recommendations (duration in min/week, frequencies/week).

We will perform a subgroup analysis based on age groups to test the secondary hypothesis that compliance in older group is better with the Otago compared to T&E and that in younger participants’ compliance is better in T&E compared to Otago.

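### A coordinator who knows the allocation may exclude patients from the trial with no stated fall follow-up, which sits badly with the all-randomised analysis and strains the missing-at-random assumption

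*Protocol article*

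**What the plan says.** The last paragraph of Control interventions provides that, where exercising at home might harm patients, "the local coordinator could exclude the patients of the trial". It does not say when this may happen, whether the diary and assessments continue, or how the patient's data are handled.

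Under Recruitment, randomization, blinding and treatment allocation, eligibility has its own step: "The final decision on inclusion or exclusion and randomization takes place after the baseline assessment". The randomisation "is concealed to all members of the research team", but once a patient is assigned, "The local coordinators will take note of the allocation group in REDCap". Under Outcomes, the completed diaries, which are the prospective source of the primary outcome, go to these same coordinators.

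Outcomes also covers voluntary withdrawal: "If a patient decides to stop his participation (completing monthly diaries and exercise training"), then "the physiotherapist will ask him to participate at the intermediary or/and finale assessment". Falls have a second source: "In addition, falls events (number, circumstance and severity) will be asked during the intermediary assessment and at the final assessment".

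Statistical analysis states: "We will use an intention-to-treat analysis based on all randomized patients". Missing values and dropouts are handled by multiple imputation (50 datasets, missing at random), with adjustment for length of observation, centre, age and fall-risk category. Sensitivity analyses are planned without imputation, on the missing-at-random assumption, and per protocol with time-varying covariates.

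**The concern.** Someone who knows the group and receives the fall diaries may remove a patient from the trial on a broadly worded trigger. In a falls trial, patients for whom exercise looks unsafe are plausibly those most likely to fall. Whether exercise looks unsafe may also depend on the programme. Otago exercises are prescribed by the physiotherapist, whereas T&E participants choose tasks after rating their difficulty. T&E and Otago have eight home sessions and Helsana has one, so the chances to notice a problem differ too.

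If follow-up ends at exclusion, primary-outcome data are lost selectively, and possibly to a different extent by arm. Both main comparisons are exposed: non-inferiority of T&E to Otago, and superiority of Otago to Helsana. The non-inferiority test is the more sensitive, because the stated margin is small.

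**Working it through.** **1. Is the exclusion after randomisation?** Two eligibility steps precede it: Table 1 already excludes patients with a physician's contraindication, and the final inclusion decision follows the baseline assessment. The sentence in Control interventions is separate from both, closes the description of the programmes and concerns doing the exercises. Post-randomisation exclusion is therefore the natural reading, but it is an inference because no timing is given.

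**2. Is the coordinator blind?** No. The concealment statement concerns the randomisation before assignment; the coordinator then records the group. The blinding under Outcomes applies to the assessors.

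**3. Does the plan's dropout allowance cover this?** The article gives no figure for exclusions, only 15% dropout. That allowance agrees with the stated sizes: 344 / 0.85 = 404.7, rounded up to 405, and 137 / 0.85 = 161.2, rounded up to 162. Expected losses are 0.15 × 162 = 24.3 in each large arm and 0.15 × 81 = 12.2 in the small one. The allowance protects the number of patients, not the comparability of those who remain.

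**4. How large could the effect be?** The article gives no frequency or fall rate for excluded patients, so these values are assumed. Let a fraction x of one arm be excluded, with k times the fall rate of the rest. Assume a true rate ratio of 1, no exclusions in the other arm, none of the excluded patients' data kept and no imputation. Then

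observed ratio = 1 / [(1 − x) + x·k]

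| x | k = 2 | k = 3 |
|---|---|---|
| 2% | 1/1.02 = 0.98 | 1/1.04 = 0.96 |
| 5% | 1/1.05 = 0.95 | 1/1.10 = 0.91 |
| 10% | 1/1.10 = 0.91 | 1/1.20 = 0.83 |

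Five per cent of a large arm is 0.05 × 162, about 8 patients.

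**5. Comparison with the margin.** Sample size gives a margin of 5% without a scale. If it is relative, excluding 5% of one arm produces a shift of about the same size (k = 2) or somewhat larger (k = 3).

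**6. Direction.** Exclusions only in T&E would favour T&E over Otago. Exclusions only in Otago would work against T&E and would favour Otago over Helsana. Equal exclusions in T&E and Otago would cancel between those two arms (0.95 / 0.95 = 1).

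**The case against.** The strongest reply is that the article never says excluded patients leave the analysis. Read with the Statistical analysis section, a randomised patient who is excluded remains in the analysis set, with missing data imputed and the observed time counted. The plan also tests the missing-at-random assumption and names differential censoring as a bias to be reduced, although only for the per-protocol analysis. This stands in part: the illustration above omits these safeguards and is a worst case of its kind. They do not settle the matter. Adjusting for length of observation does not help if the unobserved months carry a higher rate, and imputation recovers only the excess risk that the recorded variables predict.

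Two stronger readings are tempting and are not supported.

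- A reader might infer that stopping the exercises also stops the fall diary. Outcomes does not say this. It describes a patient who chooses to end both. Such a withdrawal creates missing data and does not itself break intention-to-treat, and falls are asked again at 6 and 12 months of those who attend. What remains is that no route is described for stopping exercise while keeping the diary.
- A reader might infer a bias of twice the margin. If the 5% excluded from T&E fall at three times the assumed arm rate of 0.5, then 0.50 = 0.95y + 0.05 × 1.5 gives y = 0.447, a ratio of 0.895. The arithmetic is right. The conclusion, however, needs exclusions in T&E only, all their data discarded, no imputation, an assumed threefold rate and a relative margin, and the documents establish none of these.

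**Conclusion.** The point holds as an inconsistency with a plausible bias, not as a demonstrated breach of intention-to-treat. As written, a coordinator who is not blind may exclude patients from the trial on grounds plausibly linked to fall risk and programme, with no continued fall follow-up stated. Control interventions and Statistical analysis must be reconciled. Under the assumptions shown, 5% selective exclusion from one arm gives a ratio of about 0.95 to 0.91. The actual effect would be smaller to the extent that data before exclusion are kept, imputation works or exclusions are balanced. The conclusion rests on the post-randomisation reading; if the sentence concerns only eligibility before randomisation, the article should say so and the concern falls away.

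**What to change.** In Control interventions, replace exclusion from the trial by a statement that ending the exercise programme on safety grounds does not end trial participation. The patient is asked to continue the monthly fall diary to month 12 and to attend both assessments, and is analysed in the group to which he or she was randomised. Say the same under Statistical analysis, so that the two sections agree.

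In Outcomes, record stopping exercise and stopping diaries as separate events, each with date and reason, and report them by arm. Ask everyone who stops exercising to keep the fall diary.

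Who ends the exercises, and when, is unchanged. The cost is an amendment to the wording, a withdrawal form with two boxes instead of one, and a few more diaries to collect.

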### Outcomes

The primary outcome “falls incidence” and exercise frequency will be assessed prospectively and for twelve months with self-recorded monthly diaries. If a patient decides to stop his participation (completing monthly diaries and exercise training), the physiotherapist will ask him to participate at the intermediary or/and finale assessment. Physiotherapist-assessors who are unaware of group allocation (“blinded assessors”) will assess the secondary outcomes at baseline, at the six-month intermediary assessment, and at the twelve-month final assessment. All assessors are independent physiotherapists and specially trained to perform the assessments.

To ensure that the assessors remain unaware of the group allocation, patients are told not to talk about their treatment with the assessor.

The main outcome is the incidence of falls for twelve months. For this study we define a fall as “*an unexpected event in which the participant comes to rest on the ground, floor, or lower level, with or without injury*” as recommended in the systematic review of Hauer et al. [59]. The history of falls (number, circumstance (Where? *Inside OR outside;* When? *Day OR night;* How? *Describe shortly the event*) and severity) in the previous twelve months will be assessed at baseline. During the study, falls will be prospectively self-reported (number, date, circumstance and severity) in monthly diaries [60]. To ensure that the patients complete the diaries, the physiotherapists will check them at each visit and ask about the diaries during each phone call [59]. In addition, falls events (number, circumstance and severity) will be asked during the intermediary assessment and at the final assessment. The diaries will be sent to the coordinators. The coordinators will send them in PDF version to the project-assistant. She will enter the data in REDCap software once a month.

Secondary outcomes include severity of falls, fear of falling, gait, strength and balance and quality of life. They will be assessed at baseline, at the intermediary assessment and at the final assessment. They also include exercise-adherence. This outcome will be assessed at twelve months.

The severity of falls will be self-reported in the monthly fall diaries using the four categories defined by Schwenk et al. [61]: a. Serious injury (requiring accident and emergency or inpatient treatment); b. Moderate injury (requiring a medical/health professional examination); *C. minor* injury (reduction in physical function for at least three days); d. No injury.

Fear of falling will be measured on a visual analogic scale (0 = no fear at all to 10 = extreme fear) [19, 62] and on the Falls Efficacy Scale-International FES-I [63]. FES-I measures the level of concern about falling during social and physical activities of daily living, inside and outside the home whether or not the person actually does the activity. This 16-item questionnaire offers a response format consisting of 4 levels ranging from “*not at all concerned*” to “*very concerned*”. It is a valid and reliable tool showing a good sensitivity to detect changes in concerns about falling [64]. The score ranges from 16 to 64: the higher the score, the more concerned one is about falling.

Gait, strength and balance will be assessed with five tests of which the three first are recommended as part of the STEADI initiative of the Centers for Disease Control and Prevention (CDC) [65]:The “Timed Up and Go” test (TUG) [66–68] assesses lower extremity function, mobility and fall risk. It is not only associated with motor performance but also with cognitive function [69]. It is associated with history of past falls, but its predictive ability for future falls is limited [70] so it may be used in combination with other tests in fall risk assessment [71]. Patients sit on a chair and on the command “Go”, they have to stand up, walk three meters at a comfortable and sage pace, turn, walk back to the chair and sit down. The time is measured in seconds, begins at “Go” and ends when the patient is seated. The patients will perform the task twice. The average of both scores will be used in the analysis.The “Four-Test balance scale” [72], also called “Four Stage Balance Test” (FSBT) by the CDC, consist of standing in four progressively more difficult stances: 1. Feet side-by-side; 2. Partial tandem; 3. Tandem and 4. On one foot. If the patient can hold a position for ten seconds without moving his/her feet or needing support, he/she goes on the next position. If not, the test is stopped. The level reached will be noted.The “Five Time Sit to Stand” test (FTSTS) was described to test the ability to rise from a chair in a short battery of physical-performance tests [73]. It is a valid measure of dynamic balance and functional mobility in older adults and has excellent relative and absolute reliability and reproducibility [74]. With a cut-off value at 12 s it demonstrates a reasonable sensitivity and specificity in identification of multiple fallers [75]. Patients sit on a straight-backed chair placed next to a wall; they will be asked to fold their arms across their chest and to stand up five times in a row as quickly as possible, when the assessor says “Go”. Patients have to come to a full standing position each time they stand up and have to sit down without touching the back of the chair. The time is measured in seconds, begins at “Go” and ends with the fifth seat. The patients will perform the task twice. The average of both scores will be used in the analysis.The “Functional Reach” test (FR) [76–78] was designed to identify frail older people and elders at risk of falling. It measures the maximal distance that a person can reach forward while standing. The patient will stand next to a wall with the ipsilatéral arm at 90° flexion with fingers extended. The assessor will mark a point where the third finger is at the initial position on a static squared paper against the wall. The command is “*Lean forwards as fare you can without taking a step, bending the knee or raising the heels to bring your hand forward as far as possible*”. At the maximal anterior leaning position, the assessor marks a second point. The horizontal distance between the two points will be measured in centimetres. The patients will perform the task three times. The average of the three scores will be used in the analysis.The “Six-meter-walk” test (SMWT) will be used to assess gait speed. Patients will walk “*as fast as possible without running*” ten meters including 2-m approach, 6-m for the time measure and 2-m beyond the measure to ensure a constant walking speed across six meters [79–81]. The time will be measured in seconds and divided by 6 to calculate the gait speed in m/s. The patients will perform the task twice. The average of both measures will be used in the analysis.

Quality of life will be measured with the French and German version of the “Older People’s Quality of Life Questionnaire” OPQOL-35 [82]. The questionnaire consists of 35 items measuring quality of life based related to eight domains: 1: Life overall (4Q), 2: Health (4Q), 3. Social relationships (8Q), 4: independence, control over life, freedom (5Q), 5: home and neighbourhood (4Q), 6: Psychological and emotional well-being (4Q), 7: Financial circumstances (4Q) and 8: Culture and religion (2Q). The score ranges from 35 to 175: as higher the score, as better the quality of life.

Adherence to exercise will be prospectively assessed in monthly training diaries during 12 months where date, duration, type of exercises (including walking) and intensity of effort are noted. To ensure that the patients complete the diaries, the physiotherapists will check them at each visit and ask about the diaries during each phone call.

Confounding factors, like life situation, living place, physical activity habits and comorbidity will be documented at each assessment session.

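### Fall-diary checks follow the treatment schedule (8 visits and 4 calls in T&E and Otago, 1 visit and 4 calls in Helsana), so falls in months 1–6 are likely to be captured less completely in Helsana

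*Protocol article*

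**What the plan says.** The Outcomes section states that falls "will be assessed prospectively and for twelve months with self-recorded monthly diaries". Completeness of the diaries is secured because "the physiotherapists will check them at each visit and ask about the diaries during each phone call". The same section names blinded assessors for the secondary outcomes. It adds that falls are also asked about at the intermediary and final assessments, and that the diaries go through the coordinators to the project assistant, who enters them monthly.

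The number of visits and calls depends on the arm:

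- **T&E** (Experimental intervention): delivery "is planned with eight physiotherapy sessions and four phone calls in six months".
- **Otago** (Control interventions): "eight home session and four phone calls in six months".
- **Helsana** (Control interventions): "Physiotherapists will demonstrate the programme during one home session", and then "They will then call the patients four times in a six-week interval, to ask if they encounter problems with the exercises".

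For T&E and for Otago the text also makes diary checking part of every session. In the Otago wording, physiotherapists "verify that the diaries are correctly completed and repeat the recommendations for the training". The Helsana description has no such sentence.

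Under Data management, the project assistant verifies all entries and asks for missing data. Under Statistical analysis, the primary model adjusts for length of observation, and missing values are multiply imputed under missing at random, with sensitivity analyses.

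**The concern.** The effort made to find falls should not depend on the arm. Here it does, because the stated means of securing the diary is the treatment contact, and two programmes have many more visits than the third. The physiotherapists who prompt are those delivering the programme, so they necessarily know the allocation. The blinding of the assessors does not reach this step.

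The stake is the Otago versus Helsana comparison. The hypothesis in the Background requires Otago to be superior to usual care, and Statistical analysis lists this among the claims to be shown simultaneously. The planned contrast is small (0.79 against 0.92 falls), so modest under-recording in Helsana would remove a substantial part of it. Helsana is also the smallest arm, with 81 of 405 participants.

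**Working it through.** **Contacts at which the diary is checked or asked about**

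| Arm | Visits | Calls | Total |
|---|---|---|---|
| T&E | 8 | 4 | 12 |
| Otago | 8 | 4 | 12 |
| Helsana | 1 | 4 | 5 |

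The ratio is 12/5 = 2.4. Calls are equal, so the whole difference is 8 − 1 = 7 visits. Helsana's one visit is the demonstration that precedes the calls, when there is probably little diary to check. The six-week wording for the Helsana calls could mean one call every six weeks (4 × 6 = 24 weeks) or four calls within six weeks. The count is 4 either way, and on both readings no arm has programme contacts scheduled in months 7–12.

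**What the other safeguards can reach**

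- The missing-data query acts on absent entries. A returned diary with a fall left out has nothing visibly missing.
- Adjustment for observation time and multiple imputation deal with months that are missing. An unrecorded fall in a returned diary enters the data as no fall.
- The 6- and 12-month fall questions are the same in all arms and may recover some falls, but they rely on long recall.

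**Planned effect** (Sample size section)

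Otago/Helsana rate ratio = 0.79/0.92 = 0.859; ln(0.859) = −0.152.

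**Illustration of the bias**

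Let c be the fraction of falls recorded in Helsana relative to Otago. The protocol gives no value, so c is assumed. It covers only falls left out of returned diaries, not missing diary months. With falls spread evenly over the year and the deficit confined to months 1–6:

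observed Helsana rate = 0.92 × (1 + c)/2

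observed ratio = 0.79 / observed Helsana rate

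share of log effect lost = 1 − ln(observed ratio)/ln(0.859)

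| c | Observed Helsana rate | Observed ratio | Log effect lost |
|---|---|---|---|
| 0.95 | 0.897 | 0.881 | 17% |
| 0.90 | 0.874 | 0.904 | 34% |
| 0.85 | 0.851 | 0.928 | 51% |
| 0.80 | 0.828 | 0.954 | 69% |

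For c = 0.90: 0.92 × 0.95 = 0.874; 0.79/0.874 = 0.904; 1 − (−0.101)/(−0.152) = 0.34.

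The planned difference vanishes when (1 + c)/2 = 0.859, that is c = 0.717, or about 28% under-recording in months 1–6. If the deficit lasted all twelve months, it would vanish at c = 0.859, or about 14%.

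**The case against.** **Capture is not documented as unequal.** A reader might infer that falls are in fact counted less completely in Helsana. The protocol gives no capture rate and does not show this. What it shows is unequal checking effort, from which unequal capture is a likely consequence of unknown size. This part of the objection stands.

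**Several safeguards are equal across arms.** The monthly flow of diaries to the project assistant, the query on missing data and the fall questions at both assessments apply to everyone. The analysis also allows for missing months. These narrow the problem, and they mean the illustration must not be read as the effect of missing diaries. They do not reliably reach a fall omitted from a returned diary.

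**The calls do not differ.** It is tempting to read the Helsana calls as confined to exercise problems and the others as covering diaries. But the T&E and Otago calls are also described only in terms of exercises, difficulties and encouragement, and the Outcomes sentence on asking about diaries by telephone is not limited to any arm. The calls should be treated as equal.

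**Scope is limited.** T&E versus Otago, which carries the non-inferiority test and the superiority test that follows, has identical scheduled contacts. T&E versus Helsana is not listed as a primary test. In Otago versus Helsana the bias works against the trial's hypothesis, so the risk is a missed difference rather than a false claim of benefit. All of this stands.

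**Adverse events have other routes.** A reader might infer that their reporting depends on the same visits. Under Adverse events, the patient, family and any caregiver may also report, so visits are only one route. Unequal visits can still affect the comparison of groups, but only in part.

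**Removing physiotherapist checks could lower capture** in 162 + 162 = 324 of 405 participants. This is a fair warning, so the fix should add a uniform central process and need not forbid checks at visits.

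**Conclusion.** The concern holds for one primary comparison. The protocol ties the checking of the primary-outcome diary to contacts that number 12, 12 and 5, with 8, 8 and 1 in person, and falls in months 1–6 are likely to be captured less completely in Helsana. Otago versus Helsana is exposed, with bias towards no difference. T&E versus Otago is not affected by this mechanism.

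The size is unknown. At an assumed 10% under-recording in months 1–6, about a third of the planned log effect is lost; at 20%, about 69%. These figures rest on falls spread evenly over the year, full relative capture in Otago, the planning rates of 0.79 and 0.92, and no recovery through the assessment questions. The documents do not support reading them as estimates of what will happen, or extending them to the non-inferiority result. This should be corrected, because the step concerns the primary outcome and the remedy is cheap.

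**What to change.** In the Outcomes section, make the ascertainment of falls identical in all three arms. The project assistant sends every participant the same monthly fall reminder on the same schedule, and the same query when a diary is missing or unclear. State that this central contact, not the treatment visits, is the means of securing the fall count. The programme schedules need not change.

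Ask about adverse events in the same way in all arms at the 6- and 12-month assessments.

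Report diary return by arm. Add a supportive analysis of falls in months 7–12, when no programme contacts are scheduled. Note that it estimates a later-period effect, so it cannot by itself separate ascertainment bias from a waning or delayed treatment effect.

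The cost is modest: a standard reminder and query list for existing staff, one added question at two existing assessments, and one further analysis of data already collected.
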